## Abstract

**Background:**

In the Netherlands, suicide rates showed a sharp incline and this pertains particularly to the province of Noord-Brabant, one of the southern provinces in the Netherlands. This calls for a regional suicide prevention effort.

**Methods/design:**

Study protocol. A regional suicide prevention systems intervention is implemented and evaluated by a stepped wedge trial design in five specialist mental health institutions and their adherent chain partners. Our system intervention is called SUPREMOCOL, which stands for Suicide Prevention by Monitoring and Collaborative Care, and focuses on four pillars: 1) recognition of people at risk for suicide by the development and implementation of a monitoring system with decision aid, 2) swift access to specialist care of people at risk, 3) positioning nurse care managers for collaborative care case management, and 4) 12 months telephone follow up. Eligible patients are persons attempting suicide or expressing suicidal ideation. Primary outcome is number of completed suicides, as reported by Statistics Netherlands and regional Public Health Institutes. Secondary outcome is number of attempted suicides, as reported by the regional ambulance transport and police. Suicidal ideation of persons registered in the monitoring system will, be assessed by the PHQ-9 and SIDAS questionnaires at baseline and 3, 6, 9 and 12 months after registration, and used as exploratory process measure. The impact of the intervention will be evaluated by means of the RE-AIM dimensions reach, efficacy, adoption, implementation, and maintenance. Intervention integrity will be assessed and taken into account in the analysis.

**Discussion:**

The present manuscript presents the design and development of the SUPREMOCOL study. The ultimate goal is to lower the completed suicides rate by 20%, compared to the control period and compared to other provinces in the Netherlands. Moreover, our goal is to provide specialist mental health institutions and chain partners with a sustainable and adoptable intervention for suicide prevention.

**Trial registration:**

Netherlands Trial Register under registration number NL6935 (5 April 2018). This is the first version of the study protocol (September 2019).

## Background

Completed suicides and suicide attempts c physical and emotional harm on the individual. Significant others, the community, and even entire nations suffer the consequences of such tragic events [1, 2]. Annually, more than 800,000 suicides occur worldwide, of which over 56,000 were reported in the European Union (EU), and almost 2000 in the Netherlands [1, 3, 4]. Although suicide rates in the Netherlands were equal to the EU-average [3], they did show a sharp incline of 37% between 2007 and 2013 [4]. This might be related to the economic recession in 2008 and rigorous budget cuts in the mental health sector [5, 6]. Since 2013, the relative suicide rate in the Netherlands has been stable, without decreasing [4]. In Noord-Brabant, one of the twelve provinces of the Netherlands, this stabilization in the suicide rates did not take place, as the absolute number of suicide in this province increased by 64%. Remarkably, 30% of this 64% increase in completed suicides happened in the years after 2013 [4]. At the start of the grant application for this study in 2015, Noord-Brabant even ranked second nationally over the five previous years (2010–2014) and there were 293 suicides in 2014, which is 11,5 suicides per 100,000 residents [4]. This poses a problem in the Netherlands and more specifically a regional problem in Noord-Brabant.

An important issue in effective suicide prevention is that approximately two-thirds of suicide victims were not receiving mental health care [7, 8], while they were probably in need of it, as suicide occurs mostly in the context of mental disorders [1, 2]. This might be due to a lack of visibility of people at risk, as help-seeking behaviour for suicidality is low, possibly due to stigma and poor suicide literacy [9]. Moreover, transitions of and discharges from care are associated with an increased risk of suicide attempt or death [10, 11]. An exploration amongst stakeholders identified that a tentative explanation might be a lack of communication between health care providers of different institutions or lack of swift entry into specialist care due to logistical barriers and waiting lists.

Another problem concerns the identification of people at risk for suicide since there are many risk factors known that are also very common [2]. Suicide attempts and suicidal ideation are among the strongest predictors of completed suicide [1, 12]. Suicide risk is also elevated in case of job and financial problems, unbearable mental pain, lack of a support system, trauma, stigma, impulsive aggression, hopelessness, living alone, and being faced with loss [1, 2, 13]. In addition, suicide occurs more often in males than in females [1]. The predictive power of these individual risk factors is thus very low [2, 14]. There is yet no single tool, questionnaire or instrument that can predict suicide [15]. Clinical assessment can also be very hard, given the fact that about 45% of patients who died by suicide did meet with a primary care provider in the preceding month [7]. A large (*N* = 4800) longitudinal study found that prediction failed mostly, as 60% of patients that died by suicide had been categorized before as low risk by mental health professionals [16]. In the Netherlands, a Multidisciplinary Guideline Diagnostics and Treatment of Suicidal Behaviour (MGSB) was developed in 2012 [17]. A subsequent study aimed at training professionals for the assessment and treatment of suicidal behaviour -as recommended in this MGSB- resulted in greater guideline adherence, but did not result in lower suicide rates in the Netherlands so far [18].

This urgently calls for a suicide prevention effort in Noord-Brabant, aiming to reduce suicide by identifying people at risk for suicide and by a collaborative effort to improve the delivery of services by all relevant stakeholders.

## Rationale

This study considers completed suicides as mostly preventable deaths and in that vein will follow an example of a regional systems intervention study of preventable deaths in traffic trauma-related mortality in Orange County, USA [19]. A regional network of Specialty Mental Health Institutions, general hospitals, general practices, public health partners and community partners (schools, railway services, municipalities, agricultural organizations) will be implemented with the aim to diminish preventable deaths by suicide in Noord-Brabant. Our suicide prevention system is called SUPREMOCOL, which stands for Suicide Prevention by Monitoring and Collaborative Care, and is based on four pillars: [1] recognition of people at risk for suicide development and implementation of a monitoring system with decision aid, [2] swift access to specialist care of people at risk, [3] positioning nurse care managers for collaborative care case management, [4] and 12 months telephone follow up.

## Objectives

The aim of the present paper is to describe the content of the SUPREMOCOL regional systems intervention and the study design for the scientific evaluation. The four pillars of the intervention are described in the paragraph ‘Intervention’ and the hypothesis for the scientific study in the paragraph ‘Scientific evaluation’. The objective of the SUPREMOCOL project is to lower suicide rates in the province of Noord-Brabant, the Netherlands, by 20%. To this end, three sub-objectives are essential:
Establishing the SUPREMOCOL systems intervention, for persons at risk for suicide by improving delivery of services by a well-functioning chain of care on multiple levels, set up with the purpose to remain available after ending of the study.Evaluate the effect of this multilevel suicide prevention systems intervention in terms of completed suicides and non-fatal suicide attempts in an embedded evaluation.Explore the public health impact of the suicide prevention intervention by the RE-AIM framework, including which factors (i.e. patient or transition factors) are associated with early withdrawal of treatment, taking the relevant stakeholders i.e. professionals, patients and their significant others into account.

## Methods/design

### Intervention

#### Framework

In the development of our suicide prevention intervention we were inspired by a successful systems intervention, that aimed to improve access to care by the regionalization of trauma care for preventable traffic trauma-related deaths in Orange County, California [20]. A combination of swift triage and entrance to designated expert trauma care led to a decrease to one-eighth of the previous rate of preventable deaths, i.e. deaths that could have been prevented by better delivery of services [21]. Similar effects were found in several other regions implementing the same systems intervention [22]. Several key components of the intervention of West and colleagues [23, 24], were translated to our specific target group and context. One component is to work with the concept of preventable death; as in the case of traffic trauma, not all suicides may be preventable. This can, for example, be the case in people experiencing unbearable suffering and suicidality due to severe mental disorders combined with debilitating somatic illness. For our systems intervention, we deemed suicides preventable if they could be prevented by better delivery of services. For example, if someone experiences suicidality due to a psychiatric disorder which has been intensively -but yet unsuccessfully- treated in primary care, a completed suicide might be prevented by swiftly transferring the person to specialist mental health care. This view has been advocated by Wasserman et al. (2016), who coined a completed suicide with the term unnecessary death [25]. Another component is to do first triage on the spot by field professionals if indeed a preventable death is the case. Moreover, providing trauma treatment, not at the closest emergency room, but at the emergency room where an experienced trauma team is available is also an important component. This has been proven to be more effective despite the initial time loss outside the hospital, due to the high efficiency in the trauma specialist center, once the patient arrives there [20]. Establishing swift access to specialized trauma care in the institution itself in a practical manner could also be translated into our approach. Our suicide prevention system is called SUPREMOCOL, which stands for Suicide Prevention by Monitoring and Collaborative Care, and focuses on four pillars.

### Pillar 1: development and implementation of a monitoring system with decision aid

The first pillar concerns developing and implementing a monitoring system with decision aid to support professionals in reporting, assessing and monitoring people at risk for suicide. By using this system, we expect to identify more people at risk for suicide and to provide a tool for suicide risk assessment. In the monitoring system, both (mental) health care and non-(mental) health care professionals are involved to signal people at risk and to refer them to the closest specialist mental health care institution (SMHI). A decision aid is built-in to support health care professionals in methodical/systematic, evidence-based suicide risk assessment. The decision aid for suicide risk assessment consists of two parts: the Patient Health Questionnaire-9 (PHQ-9) and an additional risk assessment tool that is developed by the project group. The PHQ-9 is a reliable and valid measure of depression severity and has been proven useful in both clinical and research practice [26]. In this study, the Dutch translation is used. The scores comprise the time period over the last 2 weeks and are 0 (not at all), 1 (several days), 2 (more than half of the days), and 3 (nearly every day) [26]. Item 9 of the PHQ-9 questionnaire had been found to be a robust predictor of suicide attempts and deaths, regardless of age [27], therefore, item 9 is used in this study as a first screener for suicidality. In this item, the person scores how often he/she is bothered by ‘Thoughts that you would be better off dead, or thoughts of hurting yourself in some way’ [26]. Although the whole PHQ-9 questionnaire will be filled out, suicide risk will be only calculated based on the score on item 9. If a person scores ‘0’ or ‘1’ on this item, suicide risk is considered as *low* risk, while the suicide risk is considered as a *medium* to *high* if a person scores ‘2’ or ‘3’. If the risk is medium or high, a second screener will follow to further estimate the suicide risk, which is the decision aid. This decision aid is developed by the project group and is based on seven questions for suicide risk which are answered with ‘yes’ or ‘no’ and is provided in Table 1.

**Table 1 Tab1:** Decision aid

Domain	Question
In the past month	1. Did you have thoughts of being better off when you were dead or did you wish you were dead?
	2. Did you want to hurt yourself?
	3. Did you have thoughts about suicide?
	4. Did you make suicide plans?
	5. Did you attempt suicide?
In life	6. Did you have thoughts of being better off when you were dead or did you wish you were dead?
Clinical impression	7. Is there any acute danger in the behaviour of the person?

Based on the answers of the person, suicide risk is calculated, which can be either high, moderate or low. The suicide risk is estimated as *high* if the person answers ‘yes’ on question 4 or 5, or on both questions 3 and 6, or if question 7 is answered by the clinician with ‘yes’. If the person answers ‘yes’ only on question 3, or only on questions 2 and 6, the estimated risk is *moderate*. The suicide risk is otherwise estimated as *low* risk. This algorithm is visually displayed in Fig. 1. In the monitoring system, a cut-off is used, in which a moderate and high estimated risk are both labelled as ‘increased risk’.

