### Target population

The target population for the intervention are people that present themselves to, or are identified by, a professional of one of the participating institutions by showing signs of suicidal behavior. In this study, suicidal behavior includes both suicidal ideations and actions -preparatory and attempting- that are undertaken with the intention to die [17]. Inclusion criteria for registration in the monitoring system are 1) having a medium to high suicide risk according to the decision aid (see paragraph ‘Framework’ for the decision aid), 2) being a resident of the province of Noord-Brabant, and 3) giving permission to be registered in the monitoring system. People will be excluded if 1) low suicide risk is assessed, 2) they are not living in Noord-Brabant, and/or 3) they do not give consent to be registered in the monitoring system.

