### Step 1: registration in the monitoring system

In our systems intervention, both (mental) health care professionals - such as emergency room physicians, general practitioners or school psychologists - as well as non-health care professionals - such as railway professionals - can signal people at risk and register them in the monitoring system. When participating professionals signal people at risk, they first ask them for permission for registration in the monitoring system (according to the European Union General Data Protection Regulation [GDPR]). When permission for processing personal data is given, professionals who work as a (mental) health care professional perform a suicide risk assessment via the decision aid, which is built-in the monitoring system. The decision aid provides feedback based on the input provided by the persons’ answers on a questionnaire and observations made by the professional. If the suicide risk is *low* according to the decision aid, the person will not be registered and the professional is advised to refer the person to his/her general practitioner. If the suicide risk is *medium* or *high*, the person will be registered in the monitoring system, and their registration is automatically sent to the nearest SMHI, this is based on the postal code of the person who will be registered. Professionals that do not work in (mental) health care do not perform a suicide risk assessment as they are not authorized and trained to do so. They will register people in the monitoring system based on their own estimation. In these cases, the risk assessment will be performed later on by the SMHI crisis care professional who can use the decision aid to do so.

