“Success rate if implemented as in guidelines; defined as positive outcomes minus negative outcomes” [43]	Pillar 1: monitoring system Pillar 2: swift access Pillar 3: collaborative care Pillar 4: 12 months follow up	• Changes (both positive and negative) in primary and secondary outcome measures (suicidal behaviour), as described in the Methods section	• National and regional health records • PHQ-9 • SIDAS • Monitoring system
		• Experiences of patients and professionals regarding facilitating or hindering factors, as described in the Methods section	• Online surveys • Regular meetings
Adoption			
“Proportion of settings and practices that will adopt this intervention” [43]	Pillar 1: monitoring system	• The number (+ characteristics) of chain partners that made use of the monitoring system versus the number of chain partners who have received an account to this system	• Monitoring system
		• The number (+ characteristics) of SMHI professionals that made use of the monitoring system versus the number of SMHI professionals who have received an account to this system	• Monitoring system
	Pillar 2: swift access	• The number of SMHI departments that have the intention to provide swift access versus the total number of participating SMHI departments	• SMHI
	Pillar 3: collaborative care	• The number of SMHI nurses that have the intention to work according to the collaborative care model versus the total number of SMHI nurses in the SMHI treatment departments	• SMHI
	Pillar 4: 12 months follow up	• The number of SMHI professionals that have the intention to provide follow up contacts versus the total number of SMHI professionals who received an account to the monitoring system	• SMHI
Implementation & Maintenance			
Implementation “Extent to which the intervention is implemented as intended in the real world” [43] Maintenance “Extent to which a program is sustained over time” [43] *Implementation and Maintenance comprise the same variables, however, Maintenance will be measured at nine months.*	Pillar 1: monitoring system	• The number of successful registrations in the monitoring system versus the total number of people attempting suicide (and were in need of an ambulance ride)	• Monitoring system • Ambulance records
		• The number of first contacts that actually took place versus the number of eligible persons for a first contact	• Monitoring system

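### As written, a PHQ-9 item 9 score of 0 or 1 ends the health care risk assessment as low before a past-month attempt or clinician-judged acute danger is asked about

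*Protocol article*

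**What the plan says.** The protocol article describes a two-stage risk assessment under Pillar 1. All of the PHQ-9 is completed, but only item 9 counts towards risk. Item 9 asks how often the person has had thoughts of being better off dead or of self-harm, and "The scores comprise the time period over the last 2 weeks". A score of 0 or 1 is low risk; 2 or 3 is medium to high. The second stage depends on the first: "If the risk is medium or high, a second screener will follow to further estimate the suicide risk, which is the decision aid".

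That second stage is the list of seven yes/no questions in Table 1. Questions 1 to 5 cover the past month, and the fifth reads "5. Did you attempt suicide". Question 7 is the clinician's impression of acute danger. In the algorithm below the table, a yes on question 4 or 5 is enough for high risk, as is a yes on both 3 and 6, "or if question 7 is answered by the clinician with" a yes.

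Under Step 1 (registration in the monitoring system), when a health care professional finds low risk, "the person will not be registered and the professional is advised to refer the person to his/her general practitioner". The section on target population lists low risk as an exclusion. Professionals outside health care register on their own estimate, and the specialist mental health institution assesses risk later.

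On who the intervention is for, the abstract states: "Eligible patients are persons attempting suicide or expressing suicidal ideation". The section on target population says that "suicidal behavior includes both suicidal ideations and actions -preparatory and attempting- that are undertaken with the intention to die".

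**The concern.** The two facts that the algorithm treats as decisive on their own, a recent attempt and visible acute danger, are asked about only after a filter that looks at neither. Item 9 measures how often thoughts occurred over two weeks. It does not ask about attempts, and it leaves no room for the clinician's observation.

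The affected cases are easy to picture. Someone who attempted three weeks ago and has had no such thoughts since scores 0. Someone who attempted last week after thoughts on several days scores 1. A clinician may see acute danger in a person who denies such thoughts; that person scores 0, and question 7 is never reached.

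At stake is access to the added care: daily contact attempts by the crisis team, swift access, and a year of telephone follow-up. The article's own rationale says that these people need it. The Background section names attempts among the strongest predictors of suicide and cites a study in which 60% of patients who died by suicide had earlier been classed as low risk. The section on Pillar 2 puts risk after a previous attempt at thirty times higher.

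**Working it through.** The article gives no figure on this point to reproduce, so the check follows the written rule through every case.

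**Inputs**
- Gate (Pillar 1): item 9 of 0 or 1 gives low and stops; 2 or 3 leads to the seven questions.
- High-risk rule (text below Table 1): yes on 4, or on 5, or on 7, or on both 3 and 6.
- Consequence of low (Step 1; Target population): no registration.

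**Answer patterns**
1. Seven yes/no questions give 2^7 = 128 patterns.
2. A pattern is not high only if 4, 5 and 7 are all no and 3 and 6 are not both yes. Questions 1 and 2 are free (2 × 2 = 4 combinations) and 3 of the 4 combinations of questions 3 and 6 remain: 4 × 3 = 12.
3. High patterns: 128 − 12 = 116.
4. Patterns with a yes on 5 or 7: 128 × (1 − 1/2 × 1/2) = 96. All 96 are high.
5. If a yes on question 1 (past month) is taken to entail a yes on question 6 (in life), 96 coherent patterns remain. Of these 88 are high, and 72 of the 88 have a yes on 5 or 7.

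**Effect of the gate, on all 128 patterns**

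| Item 9 score | Profiles (2 scores × 128) | With yes on 5 or 7 | Of these, rated high |
|---|---|---|---|
| 2 or 3 | 256 | 192 | 192 |
| 0 or 1 | 256 | 192 | 0 |

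The same 192 profiles move from high to low through the item 9 score alone. These are counts of logical profiles, not of patients.

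**Time windows**
Item 9 covers 14 days and question 5 covers a month. With a 30-day month, 30 − 14 = 16 days, or 16/30 = 53%, of the period in question 5 lie outside that of item 9 (14/28 = 50% for 28 days, 17/31 = 55% for 31). This shows how the two answers can differ; it does not show how often they do.

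**Could another reading rescue the rule?**
The article uses the term decision aid both for the two-part tool (PHQ-9 plus questions) and for the seven questions alone. On the first reading the person is low by the decision aid and excluded. On the second, the person never reaches the decision aid and so cannot meet the inclusion criterion of medium to high risk by it. Both readings end without registration. Step 1 says that feedback also draws on what the professional observes, but the only observation item described is question 7, which lies behind the gate.

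**The case against.** The strongest reply has three parts. First, the text refers to Fig. 1 for the algorithm, and that figure is not in our copy. A bypass could be drawn there. This stands as a condition on the whole point. However, the text cites Fig. 1 when it describes the seven-question algorithm, and nowhere mentions an override.

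Second, item 9 as first screener is a declared choice with a stated reason, its value as a predictor of attempts and deaths. It is also normal for inclusion criteria to be narrower than the target population, and the abstract's line is only a summary. This is fair, and it is why the point does not attack the cut-off or call the criteria contradictory. It does not explain why answers that the algorithm treats as sufficient for high risk should never be sought in someone already known to have attempted.

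Third, the harm is bounded. Someone who is not registered keeps usual care, and the professional is advised to refer to the general practitioner. The route for professionals outside health care is not gated before registration. All of this stands.

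A reader might also infer that the gate distorts the evaluation. Table 2 includes as an implementation variable "The number of successful registrations in the monitoring system versus the total number of people attempting suicide" and needing an ambulance ride, so unregistered attempters might seem to cap that ratio and penalise sites that follow the protocol. The documents do not support this. As written, the numerator is all registrations, including people with ideation only and people entered by the ungated route, so no cap follows. The ratio is also one of 14 implementation variables. Implementation is combined with reach and adoption in the integrity score and weighted across four pillars, and nothing shows that the gate acts differently between subregions.

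**Conclusion.** The point holds for the health care route, as the text is written and provided that Fig. 1 contains no override. A score of 0 or 1 on item 9 closes the assessment as low before a past-month attempt or clinician-judged acute danger is asked about, and the person is not registered. This sits badly with a target population that expressly includes people who attempt suicide.

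Its size in patients is unknown: the documents do not say how often people score 0 or 1 after an attempt or while showing acute danger. What can be shown is that the rule, followed exactly, reverses the algorithm's own rating in every such case.

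It would be wrong to infer a flaw in the effect estimate. Completed suicides are counted in the whole population from public records, so neither the primary outcome count nor the sample size depends on who is registered. This is a matter of patient safety and of reaching the intended population, and it is worth fixing because the remedy is cheap.

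**What to change.** State in the section on Pillar 1 and again under Step 1 that a reported suicide attempt in the past month, or acute danger in the clinician's judgement, leads to the seven questions whatever the item 9 score. Leave the item 9 cut-off otherwise unchanged. Build the same bypass into the monitoring software and check that Fig. 1 shows it. If the software or the figure already works this way, only the text needs correcting.

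The cost is one sentence in each of the two sections, one rule in the software, and some extra registrations for the crisis teams. Those admitted by a confirmed yes on question 5 or 7 are people whom the article's own algorithm rates as high risk.

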### Exploratory process measure: suicidal ideation

To evaluate whether SUPREMOCOL leads to a reduction in suicidal ideation in people registered in the monitoring system, if possible, suicidal ideation will be measured by PHQ-9 and SIDAS questionnaires via an online survey. This will be measured at baseline and after 3, 6, 9 and 12 months. Suicidal ideation will also be measured by the PHQ-9 and decision aid outcomes as filled out in the monitoring system at registration, and during the monitoring contacts at 6 weeks, and 3, 6, 9 and 12 months after registration. For the latter, no extra actions from the person are requested as these questionnaires are already filled out for regular care. The Patient Health Questionnaire-9 (PHQ-9) is a reliable and valid clinical and research tool for the measurement of depression severity [26]. The Suicidal Ideation Attributes Scale (SIDAS) is a valid measure for severity of suicidal ideation [45]. Questionnaires will be as short as possible to promote participant retention and complete follow-up; the PHQ-9 questionnaire consists of nine questions and the SIDAS of five questions.

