#### Statistical methods

To examine whether SUPREMOCOL leads to a reduction of completed suicides of 20% in the province of Noord-Brabant, the total number of completed suicides in the post-measurement will be compared to the total number of completed suicides in the pre-measurement. As the total number of residents in this province might have changed, we will also compare the pre- and post-incidence rates of suicides. An exact rate ratio test will be used. To take general trends over time into account, we will compare the incidence ratio in Noord-Brabant with the incidence ratios in other provinces in Noord-Brabant, and with the other provinces combined.

To examine whether SUPREMOCOL leads to a reduction of completed suicides and suicide attempts in association with the stepwise implementation of the system intervention in the subregions of the province, the total number of completed suicides and suicide attempts in each month will be compared to the two levels of our stepped wedge trial: region and time. A poison multilevel model will be used. The occurrence of completed suicide or admissions due to suicide risk in an SMHI will also be taken into account in the analysis. The suicide rates will be corrected for seasonal fluctuations [45]. In a second model, organisational differences between the regions, such as available number of crisis departments, will be taken into account. In a third model, the level of treatment integrity per subregion will be taken into account as well.

To explore whether SUPREMOCOL leads to a reduction of suicidal ideation in people registered in the monitoring system, the scores on the PHQ-9, SIDAS, and decision aid -that will be filled out by participants during the year that they receive the Supremocol additional care- will be compared by repeated measures. This will be used as exploratory process evaluation, as there is no control group for this.

To examine the impact of SUPREMOCOL with regards to reach, efficacy, adoption, implementation, and maintenance, an impact score will be calculated for each SMHI region and time period. This scores will be based on the function of all five RE-AIM dimensions, which are represented on a 0% (no impact) to 100% (best possible impact) scale [43].

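### The decision-aid category is followed over time as a measure of suicidal ideation, but for people rated high only through a recent attempt or a clinician impression it can fall while ideation is unchanged

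*Protocol article*

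**What the plan says.** In the section on the exploratory ideation measure, the protocol states: "Suicidal ideation will also be measured by the PHQ-9 and decision aid outcomes as filled out in the monitoring system at registration". The same readings are repeated at the monitoring contacts at 6 weeks and 3, 6, 9 and 12 months. Under Statistical methods, "the scores on the PHQ-9, SIDAS, and decision aid" "will be compared by repeated measures. This will be used as exploratory process evaluation, as there is no control group for this".

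Pillar 1 defines the instrument. PHQ-9 item 9 is a first screener, and the seven yes/no questions of Table 1 follow when it scores 2 or 3. Risk is high if the answer is yes "on question 4 or 5, or on both questions 3 and 6, or if question 7 is answered by the clinician with" yes. It is moderate if only question 3, or only questions 2 and 6, are answered yes, and otherwise low. The monitoring system merges moderate and high into one increased-risk label.

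Questions 1 to 5 carry the heading "In the past month". Among them is "5. Did you attempt suicide". Question 6 asks about a death wish over the whole life. The last item is a clinical impression: "7. Is there any acute danger in the behaviour of the person".

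Under Target population the protocol itself distinguishes thoughts from acts: "suicidal behavior includes both suicidal ideations and actions -preparatory and attempting- that are undertaken with the intention to die".

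**The concern.** Two of the four routes to high are not ideation. Question 5 records an act, and attempts are already the trial's secondary outcome. Question 7 records a professional's judgement of behaviour. An outcome built on these can move for reasons unrelated to ideation.

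For question 5 the movement follows from the timetable. An attempt that prompted registration can score at registration and cannot score later, because the look-back period is shorter than the interval to the first call. A fall produced this way would be counted towards the stated hypothesis that ideation diminishes in registered people. With no control group, no comparison would remove it. The caveat about the missing control group warns of natural recovery and regression to the mean. It does not warn of an index event leaving the recall window.

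**Working it through.** The plan gives no figure on this point, so the check applies the stated rule to answer patterns.

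**Inputs.** Routes to high: Q4; Q5; Q3 and Q6 together; Q7 (Pillar 1). Recall for Q1 to Q5: past month, about 30 days (Table 1). First follow-up: 6 weeks (Step 3).

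**Window.** 6 × 7 = 42 days, which exceeds about 30. With contacts on schedule, an attempt at or before registration is outside the Q5 window at every follow-up. Only a new attempt can score.

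**Example.** At registration: item 9 = 3; Q1, Q5 and Q6 yes; the rest no. Category: high, through Q5. At 6 weeks: item 9 still 3, the same death wish, no new attempt, so Q1 and Q6 yes. No route to high or moderate is open. Category: low.

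**Enumeration, Q5 only.** Set Q4 = no and Q7 = no, and let Q1 = yes imply Q6 = yes. The pair (Q1, Q6) then has 3 possible values, and Q2 and Q3 have 2 each: 3 × 2 × 2 = 12 patterns, all high while Q5 = yes. Change Q5 to no and hold the rest:

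| Reading of the moderate rule | Stay high | Fall to moderate | Fall to low |
|---|---|---|---|
| 'only' taken literally | 4 | 2 | 6 |
| 'only' taken loosely | 4 | 4 | 4 |

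The 4 that stay high are those with Q3 = yes and Q6 = yes. Of the 8 that fall, 6 have Q3 = no and 2 have Q3 = yes with Q6 = no.

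**Restoring Q4 = yes.** This adds 12 patterns, and all stay high. The count becomes 4 + 12 = 16 of 24 staying high and 8 of 24 falling.

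**Q5 and Q7 both switched off.** With Q1 implying Q6, 72 patterns are high with Q5 and/or Q7 = yes. After the switch 48 stay high and 24 fall. The merged increased-risk label is lost in 12 of 72 (loose reading) to 18 of 72 (literal reading). Every pattern that falls has Q4 = no and lacks the Q3-and-Q6 pair.

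**From patterns to people.** Pattern counts are not patient proportions. If a share s of registered people were high only through Q5 or Q7, complete switch-off at fixed ideation would lower the high share by s: 5 points for s = 5%, 30 points for s = 30%. These values of s are assumptions, and the result only restates them.

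**The case against.** - **The falling patterns are unusual.** The protocol defines attempts as acts with intent to die. Someone who attempted suicide in the past month would normally report suicidal thoughts that month and a lifetime death wish. If Q5 = yes always implied Q3 = yes and Q6 = yes, only the 4 stable patterns would remain and nothing would fall. This stands as a reason to expect a small group. It does not empty the group, because nothing in the algorithm enforces such consistency.
- **Question 7 may change for good reason.** No section says that it cannot be rated by telephone or that it falls after registration. If acute danger has passed, a changed answer is a true change. This stands: a Q7 switch-off is an inference, whereas the loss of the index attempt from Q5 is arithmetic. What remains is that Q7 does not measure ideation.
- **A parallel series would expose the problem.** PHQ-9 is recorded at the same contacts, and in the example item 9 stays at 3. This limits the harm, but the plan still names the decision aid as an ideation measure in its own right. The online survey with SIDAS is planned only if possible.
- **The analysed variable may be settled elsewhere.** Statistical methods speaks of scores filled out by participants, which could mean item answers, and an analysis plan not shown may say so. However, the ideation section speaks of outcomes, and the only decision-aid outcome that the article defines is the category.

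A reader might infer that about two thirds of registered people (8 of 12 patterns) would appear to improve, or that any fall in the category is an artefact. The documents support neither. The 12 patterns exclude everyone with plans, patterns are not equally common, and people with Q4 = yes, or with Q3 and Q6 = yes, stay high for as long as those answers hold.

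**Conclusion.** The point holds in a limited form. The plan uses as a repeated ideation measure a category that also contains a past-month attempt item and a clinician impression. An index attempt drops out of that category by the first follow-up. For people rated high only through Q5 (or Q7), with no plans and without both Q3 and Q6 answered yes, the category can therefore fall with ideation unchanged.

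The size of this group is not stated and may be small. The conclusion rests on the algorithm as written in the text (Fig. 1 is not shown), on the category being what is analysed, and on contacts taking place on schedule. It does not rest on any assumed share of patients. The outcome is exploratory and its lack of a control group is acknowledged, so the primary and secondary analyses are unaffected.

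**What to change.** In the ideation-measure section and in Statistical methods:

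1. Name PHQ-9 item 9, recorded at registration and at every monitoring contact, and SIDAS, where the survey is done, as the measures of ideation over time.
2. Report the decision-aid category separately as a suicide-risk classification, broken down by route to high, with Q5 shown as attempts. State that a fall in the category will not be interpreted as reduced ideation.
3. Use Q1, Q3 and Q4 only as supporting description. Under Pillar 1 the seven questions follow when item 9 scores 2 or 3, so these answers may be missing for the very people whose item 9 has improved. They cannot serve as the main series.

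This does not remove regression to the mean, since item 9 is itself the entry screener. The existing caveat about the absent control group must still accompany the results.

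The cost is one fewer ideation series in an exploratory analysis. The wording changes, the data are those already planned, and the clinical use of the decision aid is untouched.
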